#### Confidentiality {27}

Information about potential participants will be collected through the personal digital patient files (case report forms), which will be used to check the patient’s eligibility to participate in this study and will not be shared. The collected personal information will be digitally stored on a secured drive, only accessible to the investigators involved in this study and by the monitor upon request.

The alphanumeric code assigned to each participant will be used for data collection to maintain confidentiality. The data that is collected in Castor EDC is not retraceable to the patient without the key file, which is securely stored with restricted access.

All forms that contain personal information, such as the signed informed consent forms, will be stored separately from the key file and coded data in a locked file cabinet.

#### Plans for collection, laboratory evaluation and storage of biological specimens for genetic or molecular analysis in this trial/future use {33}

Not applicable.

## Statistical methods

### Statistical methods for primary and secondary outcomes {20a}

The outcomes of both groups will be compared with the use of an independent samples *t*-test or a Mann-Whitney *U* test, depending on the distribution of the data, assessed using a histogram and an independent samples Kolmogorov-Smirnov (K-S test). If the data is normally distributed, an independent *t*-test will be performed, and the mean and standard deviation will be reported. If the data is not normally distributed, a Mann-Whitney *U* test will be performed, and the median and (interquartile) range will be reported.

The statistical package SPSS (version 25, IBM Corp, Armonk, NY, USA) will be used for all statistical analyses. *P*-values < 0.05 are considered significant for the primary outcome. The significance level of the secondary outcomes will be adjusted to multiple testing according to the Holm method [14].

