**Methods:**

This study is designed as a randomised controlled trial (RCT). The sample size is 270 patients, aged 5 to 17 years, with a fracture of the upper or lower extremity treated with plaster. The intervention group will be distracted with VR goggles and headphones during the replacement or removal of the plaster, whereas the control group will receive standard care. As a primary outcome, the level of anxiety will be measured with the Child Fear Scale (CFS). Secondary outcomes include anxiety reduction (difference between CFS after and CFS before plaster procedure) and Numeric Rating Scales (NRS) pain and satisfaction. Additionally, the children’s fastest heart rate during the procedure will be recorded. An unpaired samples *t*-test or a Mann-Whitney *U* test (depending on the data distribution) will be used to analyse the data.

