### Outcomes {12}

The main study outcome parameter is the difference in post-procedural anxiety scores in the intervention and control groups, using the Child Fear Scale (CFS) [15]. The secondary study parameters are the differences between the two groups in anxiety reduction (difference between the child’s CFS score pre- and post-procedural), NRS pain given by the child (pre- and post-procedure), NRS Satisfaction Score given by the child and accompanying parent/guardian and the child’s fastest heart rate measured by a finger pulse oximeter during the procedure.

The following demographic data is collected from the patient’s medical records: date of fracture, date of plaster intervention, age, sex, upper or lower extremity fracture, specific location of the fracture, type of plaster treatment (plaster replacement or removal) and previous experiences with plaster removal. After randomisation, additional demographic data is collected from the patient or accompanying parent/guardian and the orthopaedic practitioner before the plaster intervention (e.g. the use of pain killers, method of plaster removal, and the video chosen (if assigned to the intervention group)).

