### Sample size {14}

The expected anxiety score (CFS) in the control group is on average 1.78 ± 1.40 [11]. For an intended improvement by 0.5 (i.e. to 1.28) on the Child Fear Scale, with a statistical power of 80% and an alpha of 0.05, a sample size of 123 participants is needed in each group. To anticipate a 10% dropout, we will include 135 children in each group.

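### The Kolmogorov-Smirnov test named as the normality check compares the two arms with each other, and no rule ranks it against the histogram, so the primary test and summary measure are not fixed.

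*Protocol article*

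**What the plan says.** The section on statistical methods for primary and secondary outcomes {20a} of the protocol article gives one rule for all outcomes. The test is selected "depending on the distribution of the data, assessed using a histogram and an independent samples Kolmogorov-Smirnov (K-S test". The two branches are:

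- Data judged normal: a t-test for independent groups, summarised by mean and SD.
- Data judged otherwise: "If the data is not normally distributed, a Mann-Whitney *U* test will be performed, and the median and (interquartile) range will be reported"

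The Methods part of the Abstract repeats the conditional choice in short form. Under Outcomes {12}, the primary outcome is the between-arm difference in post-procedural CFS. Sample size {14} is built on means: "The expected anxiety score (CFS) in the control group is on average 1.78 ± 1.40", with a target difference of 0.5 points, leading to "with a statistical power of 80% and an alpha of 0.05, a sample size of 123 participants is needed in each group".

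**The concern.** The stated purpose of the check is to judge normality. The test named for it has a different null hypothesis: that both arms come from one common distribution, whatever its shape. A non-significant result means only that the arms look alike, and a significant one means that they differ. Neither says anything about normality.

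The same sentence adds a histogram, which does show shape. The two criteria can point in opposite directions, and the text does not say which prevails. An analyst following it must therefore use discretion, after seeing unblinded data, to decide whether the primary result is a difference in means or a rank comparison with medians. Part of the information guiding that decision is the treatment effect itself. A trial powered on a mean difference could end up not reporting one.

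**Working it through.** **1. The plan's own figure.** Inputs from Sample size {14}: difference 0.5, SD 1.40, alpha 0.05, power 80%.

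n per arm = 2 × [1.40 × (1.960 + 0.842) / 0.5]² = 123.07.

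The plan states 123, at which power is 79.98%, so the figure is reproduced. A one-sided calculation would give 97, so the design is two-sided. The quantity the trial is powered on is a difference in means.

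**2. What the named test measures.** The two-sample K-S statistic is D, the largest vertical gap between the two arms' cumulative distributions. Its large-sample 5% critical value at 123 per arm is 1.358 × √(2/123) = 0.173. No normal curve enters the calculation.

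**3. The true gap between arms.** With no effect it is 0 for any shape. At the planned effect:

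- Normal data, SD 1.40 in both arms: 2Φ(0.25/1.40) − 1 = 0.142.
- Assumed whole-number 0–4 score (the article gives no CFS range). Control probabilities 0.245, 0.221, 0.199, 0.177, 0.157 give mean 1.78 and SD 1.40. A VR arm with mean 1.28 and SD 1.40 has 0.424 at score 0, so the gap there is 0.424 − 0.245 = 0.179.
- Same control, VR-arm SD 1.20: the largest gap is at score 2, 0.824 − 0.665 = 0.159.

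These gaps lie close to the critical value, so the planned effect alone often makes the test significant.

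**4. Simulated rate of a significant K-S result, 123 per arm.**

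| Data | Effect | K-S significant |
|---|---|---|
| Normal, SD 1.40 | none | 5.5% |
| Normal, SD 1.40 | 0.5 | about 70% |
| Normal, SD 1.40 | 1.0 | 99.9% |
| Exponential (strongly skewed) | none | 5.3% |
| 0–4 score | none | 1.1 to 1.5% |
| 0–4 score, VR SD 1.40 | 0.5 | 71% |
| 0–4 score, VR SD 1.20 | 0.5 | 60% |
| 0–4 score, VR arm by exponential tilt or proportional odds | 0.5 | 51 to 53% |

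Repeat runs moved these by a few points (up to about 6% with no effect). Two sets fall outside the 50 to 71% band. A set of 300 other scenarios with the same control mean and SD gave 40 to 57%. Sliding a whole exponential distribution down by 0.5 gave 100% (gap 1 − exp(−0.5/1.40) = 0.300), but a score with a floor cannot move in that way.

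**5. Contrast with a real normality test.** A one-sample Lilliefors test on the control arm (n = 123) rejects in about 4% of runs for normal data, and in 100% for exponential data and for the 0–4 score. It follows shape; the named test does not.

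**6. Consequence if K-S alone made the choice (0–4 score, equal SDs).** Type I error is 4.9% for the rule, 4.9% for the t-test and 4.8% for Mann-Whitney; other runs gave up to 5.3% for the rule. Power is 80.8% for the rule, 78.8% for the t-test and 83.0% for Mann-Whitney; other runs put the rule at 81 to 84%. The two tests disagree on significance in about 1% of trials with no effect and about 2 to 6% at the planned effect.

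**The case against.** Four points can be made for the plan.

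- **The histogram.** A reader might infer that the treatment effect, and not the shape of the data, picks the primary test. The text does not support that. The histogram is a stated criterion and shows shape, and the branches depend on whether the data are normal, not on a K-S p-value. On a short whole-number scale, an analyst looking at a histogram would probably choose Mann-Whitney whatever K-S says. This stands. It limits the point to one part of the check, and the simulated rates describe that part only.
- **A slip of wording.** The phrase may have been carried over from the t-test named in the same sentence, with the one-sample K-S test intended. This is plausible and cannot be excluded. The name still needs correcting, because the procedure as written is the two-sample one. The missing rule for disagreement remains either way.
- **Little harm to the primary conclusion.** This stands. A reader might infer an inflated type I error or a material loss of power; the CFS calculations show neither. A loss of power on the pain or satisfaction scales might also be inferred, but the article gives no distribution for these, so any figure would rest on invented inputs.
- **The remedy exceeds the error.** Correcting the test's name and ranking the two criteria would cure the literal defect. It would leave the primary test and summary to be chosen after the data are seen, in a trial where no one is blinded, so fixing the test is the better repair at the same cost.

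**Conclusion.** The point holds in a limited form. The K-S test, as named, cannot assess normality and responds to the difference between arms: about 1 to 6% significant with no effect, and roughly 50 to 71% at the planned effect. Because its rank against the histogram is not stated, the primary test and the summary measure are not fixed in advance. That is the whole of the harm; the error rates for the primary outcome are essentially unaffected.

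The 0–4 range of the CFS and the VR-arm distributions are assumptions. The normal-data results and the no-effect exponential result do not depend on the CFS range. The conclusion about what the test compares needs no simulation. A separate statistical analysis plan, not at hand, may already fix the test; if so, the article and that plan need to be reconciled.

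**What to change.** In section {20a}, remove the K-S and histogram check as a selector and name one test per outcome before the data are analysed.

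- **Primary outcome:** Welch t-test on the difference in mean post-procedure CFS, reported with a 95% CI. This is the quantity used in Sample size {14}. Mann-Whitney U is then a stated sensitivity analysis.
- **Secondary outcomes:** one fixed test each, for example Mann-Whitney for the pain and satisfaction scales, whatever the data look like.
- **If a distribution check is kept:** a one-sample check within each arm, for description only.

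The conditional wording in the Abstract should follow. The cost is one or two sentences of amendment and one extra sensitivity analysis. Sample size and data collection do not change.

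### The normality check that chooses the primary test names a two-sample Kolmogorov-Smirnov test, which compares the arms with each other and cannot assess normality

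*Protocol article*

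**What the plan says.** In the protocol article, Statistical methods {20a}, the comparison of the groups is a t-test or a Mann-Whitney test, "depending on the distribution of the data". That distribution is "assessed using a histogram and an independent samples Kolmogorov-Smirnov (K-S test"). If the data are judged normal, "an independent *t*-test will be performed, and the mean and standard deviation will be reported". If not, "a Mann-Whitney *U* test will be performed, and the median and (interquartile) range will be reported". The rule covers all outcomes, including the primary one, which Outcomes {12} gives as the "difference in post-procedural anxiety scores in the intervention and control groups, using the Child Fear Scale (CFS").

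Sample size {14} works on the mean scale: "The expected anxiety score (CFS) in the control group is on average 1.78 ± 1.40". The target is stated as "For an intended improvement by 0.5 (i.e. to 1.28) on the Child Fear Scale", with 80% power, alpha 0.05 and 123 per group, raised to 135 for dropout.

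No other section names a one-sample K-S test or any other test of normality. The article does not say how the histogram and the K-S result are to be combined.

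**The concern.** The independent-samples K-S test takes the two randomised arms as its two samples. Its null hypothesis is that both come from the same distribution, whatever its shape. It can therefore fail in both directions. Two equally non-normal arms with no treatment effect will usually pass, and two perfectly normal arms whose means differ will often fail.

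The result feeds the choice of primary test and of the summary reported for each arm. That choice is made with the outcome data in view, in a trial in which nobody is blinded (Who will be blinded {17a}). On the non-normal branch the report would give medians, a different quantity from the mean difference behind the sample size.

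**Working it through.** **1. The plan's own figure.** Inputs from Sample size {14}: difference 0.5, SD 1.40, power 80%, alpha 0.05 (sidedness not stated).

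n per arm = 2 × (1.960 + 0.842)² × SD² / difference² = 2 × 7.849 × 1.96 / 0.25 = 123.1

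This reproduces the stated 123 with a two-sided alpha. Rounding up gives 124, and a one-sided alpha would give 97. Power at 123 per arm is 79.98%. The trial is therefore sized for a two-sided comparison of means.

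**2. What the K-S step does.** 4,000 trials per scenario were simulated with 123 per arm. The step was applied literally and without the histogram: two-sample K-S p < 0.05 leads to Mann-Whitney, otherwise to the t-test. For comparison, a one-sample K-S test with Lilliefors correction was applied to one arm (1,000 runs).

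Three shapes were assumed, because the article gives neither the range nor the shape of the score:
- a five-level 0-4 score with means 1.78 and 1.28 and SD 1.40 in both arms;
- exactly normal data with the same means and SD;
- a skewed exponential shape with scale 1.40 and a shift of 0.5, as a stress case.

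| Scenario | Two-sample K-S rejects | One-sample K-S rejects | t-test significant | Mann-Whitney significant | Literal rule significant | Two tests disagree |
|---|---|---|---|---|---|---|
| 0-4 score, no effect | 1.5% | 100% | 5.2% | 5.3% | 5.3% | 0.6% |
| 0-4 score, planned effect | 71% | 100% | 80.5% | 84.9% | 82.5% | 5.0% |
| Normal, no effect | 5.5% | 3.9% | 5.3% | 4.8% | 5.6% | 1.8% |
| Normal, planned effect | 71% | 3.4% | 81.1% | 79.3% | 81.8% | 4.9% |
| Exponential, no effect | 5.9% | 100% | 5.0% | 5.3% | 6.1% | 4.6% |
| Exponential, planned effect | 100% | 100% | 80.9% | 98.7% | 98.7% | 17.8% |

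With the 0-4 score and a smaller SD of 1.28 in the VR arm, the two-sample K-S test rejects in about 57% under the planned effect. This is the lower end of the 57% to 71% range for the ordinal and normal shapes.

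The normal rows are the clearest. The data are normal by construction, yet the named test rejects in 71% of trials once the planned effect is present. A one-sample test rejects in 3% to 4% whether or not there is an effect. The first row shows the opposite failure: clearly non-normal data go unflagged in 100% − 1.5% = 98.5% of trials.

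**3. If a one-sample K-S test was meant.** Assume that the score cannot go below zero. A normal model would then put Φ(−1.78/1.40) = Φ(−1.27) = 10% of control children and Φ(−1.28/1.40) = Φ(−0.91) = 18% of VR children below the floor. On the assumed 0-4 score the one-sample test rejects in every simulated trial, so the Mann-Whitney and median branch would be taken almost always.

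The assumed control probabilities for scores 0 to 4 are 0.245, 0.221, 0.199, 0.177 and 0.157. The cumulative probability passes one half at score 2 (0.245 + 0.221 + 0.199 = 0.665). In the VR arm, 0.424 + 0.214 = 0.638 passes it at score 1. The underlying medians are thus 2 and 1, while the means differ by 0.5. In about 22% of simulated trials the two observed medians are equal. The reported medians would then show either a full point or nothing, and not the half point that the trial was sized to detect.

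**The case against.** The strongest reply is that the criterion in {20a} is normality, and that the K-S test is only one of two tools for judging it. An analyst who looks at a histogram of a short ordinal score will probably see that it is not normal, whatever the K-S test says. This stands. The simulated percentages are rejection rates of the K-S step and not of the whole decision. A reader might infer that the treatment effect by itself selects the test, but the article does not support that. The histogram has no criterion and no rule for disagreement with the K-S result, so it softens the error without correcting it.

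A second reply is that the phrase independent samples may be a slip carried over from the t-test in the same sentence. That is possible, but nothing in the article says so. On that reading the choice would hardly vary with the data on an assumed 0-4 score, because the answer would nearly always be Mann-Whitney. What remains is the mismatch between reported medians and a sample size based on means.

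A third reply is that the damage to inference is small. This also stands. For the ordinal and normal shapes the literal rule has type I error of 5.3% to 5.6% and power close to that of either test, and the two tests disagree in about 3% to 5% of trials under the planned effect. The 17.8% disagreement belongs to an exponential shape that the article does not suggest.

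Finally, {20a} names summaries for each group and no effect estimate on either branch. The estimate and its interval may be in a fuller document, so their absence is not a finding here.

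**Conclusion.** The test is wrong as written. The named K-S test cannot do the job given to it, and no other section corrects it. Its result follows the treatment effect: about 57% to 71% rejection under the planned effect, against about 2% (assumed 0-4 score) to 6% (exactly normal data) with no effect, at 123 per arm.

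The consequence is a mis-specified, data-dependent choice of the primary test and of the summary reported. A reader might infer that the error rate or the power of the trial is compromised. The calculations do not support that: type I error is about 5% to 6% even in the skewed case, and no power is lost.

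That the named test compares the arms needs no assumption. The size of its response rests on the assumed shapes. The near-certain non-normality under a one-sample test and the 22% of trials with equal medians rest on the assumed 0-4 range, which the article does not state. Severity: should be fixed.

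**What to change.** In {20a}, delete the histogram and K-S selection rule. Name one primary analysis in advance: the difference in mean post-procedure CFS between the arms with its 95% confidence interval, from a t-test that allows unequal variances. This matches the quantity in Sample size {14}. It does not need normal data at this size: the simulated t-test level was 5.0% to 5.3% for all three shapes. Name the Mann-Whitney test as a sensitivity analysis.

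The deleted rule also governed the secondary outcomes, so state the test and summary for each of them as well.

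Baseline adjustment or a proportional-odds model may be added on other grounds, but neither is needed to cure this error.

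The cost is a change of wording in the analysis section, dated before the outcomes are analysed. Sample size, data collection and conduct of the trial do not change.

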### Interim analyses {21b}

There are no planned interim analyses.

### Methods for additional analyses (e.g. subgroup analyses) {20b}

Descriptive statistics will be provided on the baseline demographic data.

Subgroup analyses will be performed, based on age (5–11 and 12–17), sex (female and male), type of plaster treatment (plaster removal and plaster replacement), method of plaster removal (saw and scissors compared to scissors only), the extremity fractured (upper and lower extremity), the specific location of the fracture (three most frequently found fractures in this study, presumably: distal radius, hand and distal humerus) [16], the use of painkillers and previous experiences with plaster removal.

The statistical package SPSS (version 25, IBM Corp, Armonk, NY, USA) will be used for all statistical analyses.

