## Introduction

### Background and rationale {6a}

Fractures occur frequently in children; the prevalence of paediatric fractures in The Netherlands is 40% for males and 28% for females between the ages of 6 and 16 [1]. The far majority of these children receive plaster treatment. The removal of plaster is often an anxious experience for children, particularly under the age of 13 [2, 3]. Methods to effectively reduce this anxiety may improve their hospital experience.

Different methods have been investigated to reduce anxiety in children in various clinical situations. Many of these methods have proven to be ineffective, such as using midazolam [4] and showing an instructional video ahead of the procedure [5]. However, a few methods were found that reduced the anxiety: watching videos on a smartphone or tablet during the procedure [6, 7] and using noise-reducing headphones during plaster removal [2]. Virtual reality (VR) has proven to reduce anxiety and pain perception of children in other clinical situations, such as blood draws, dental procedures, intravenous injections and treatment of burns [8–12]. The use of VR may be more effective in reducing anxiety and pain perception than a tablet [7]. A pilot study on VR in the plaster room has shown promising results [13].

Therefore, the aim of this study is to further investigate the anxiety-reducing effects of VR in a large group of children with fractures who undergo plaster replacement or removal. Our hypothesis is that the use of VR will reduce the anxiety of children with fractures in the plaster room and increase their satisfaction. We also hypothesise that younger children will benefit more than older children, based on experience with ear protection [3].

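### The hypothesis that younger children benefit more is a treatment-by-age interaction, but the article names no analysis that estimates one and does not control or label the eight subgroup factors as exploratory

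*Protocol article*

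**What the plan says.** Under Background and rationale {6a} the article states a directional hypothesis: "We also hypothesise that younger children will benefit more than older children, based on experience with ear protection". Age group (5–11 and 12–17) is also the randomisation stratum (Sequence generation {16a}). The age hypothesis is not listed under Objectives {7}.

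The tests are fixed in two places. Statistical methods {20a} says "The outcomes of both groups will be compared with the use of an independent samples" t-test or a Mann-Whitney U test. The Abstract says of the same two tests: "depending on the data distribution) will be used to analyse the data". No regression model or interaction term appears anywhere.

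Methods for additional analyses {20b} lists the factors: "Subgroup analyses will be performed, based on age" (the same two groups), sex and type of plaster treatment, then "method of plaster removal (saw and scissors compared to scissors only), the extremity fractured (upper and lower extremity"), then fracture location (the three commonest sites), painkiller use and previous plaster removal. It does not name a test, say which outcomes are analysed by subgroup, or give any one factor priority.

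On multiplicity, {20a} says only this: "The significance level of the secondary outcomes will be adjusted to multiple testing according to the Holm method".

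**The concern.** A claim that one group benefits more than another concerns the difference between two treatment effects. A comparison of VR with control inside each age group gives two separate answers and no estimate of that difference. Significance in one group but not in the other can come from sampling error or unequal group size alone.

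The document fixes a hypothesis, a pair of tests, a subgroup list with cut-points, and the scope of the multiplicity adjustment. These parts do not fit together, because the tests it names cannot answer the hypothesis it states. What is at stake is a wrong claim about which children benefit. The primary comparison is not affected.

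**Working it through.** **Inputs.** From Sample size {14}: SD 1.40, effect 0.5 CFS points, alpha 0.05, power 80%, 123 per group. That gives 246 evaluable children. The article does not give the age split, so 50:50 to 70:30 (younger:older) is assumed, with the same SD in both strata.

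**1. The plan's own figure.** n per group = 2 × (1.960 + 0.842)² × 1.40² / 0.5² ≈ 123.1, which rounds up to 124 against 123 stated. It is reproduced as a two-sided calculation for the overall comparison; one-sided would give 97.

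**2. Separate tests by age, same true effect of 0.5 in both.** Power = Φ(0.5 / SE − 1.96), with SE = 1.40 × √(2/n) and n per arm within the stratum.

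| Split | n per arm, younger / older | Power, younger / older | Only younger significant | Exactly one group significant |
|---|---|---|---|---|
| 50:50 | 61.5 / 61.5 | 0.508 / 0.508 | 0.508 × 0.492 = 0.25 | 0.50 |
| 60:40 | 73.8 / 49.2 | 0.583 / 0.425 | 0.583 × 0.575 = 0.34 | 0.51 |
| 70:30 | 86.1 / 36.9 | 0.649 / 0.335 | 0.649 × 0.665 = 0.43 | 0.55 |

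The hypothesis is directional, so the relevant error is the column for only the younger group: 25% to 43%. A two-sided 5% interaction test would wrongly favour the younger group in 2.5% of such trials.

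**3. Number of strata.** Age 2, sex 2, treatment type 2, removal method 2, extremity 2, location 3, painkillers 2, previous experience 2, which sum to 17. The levels of the last two are not listed; yes/no is assumed.

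**4. Chance of at least one p<0.05 with no effect anywhere, one outcome.** Seventeen independent tests would give 1 − 0.95¹⁷ = 0.58. The strata overlap on the same children, so that is too high. A simulation of 4,000 null trials of 246 children, with assumed stratum sizes and factors independent of each other, gave 0.41. For comparison, eight independent tests would give 1 − 0.95⁸ = 0.34.

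**5. What an interaction test can do.** SE of the difference in effect = 1.40 × √(2/n_younger + 2/n_older), with n per arm in each age stratum.

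- 50:50: SE = 0.357. Power for a 0.5-point difference = Φ(0.5/0.357 − 1.96) = 0.29. Difference detectable with 80% power = 2.802 × 0.357 = 1.0 point.
- 70:30: SE = 0.390. Power = 0.25. Detectable difference = 1.1 points.

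Reaching 80% power for a 0.5-point interaction would take about 985 (50:50) to 1,172 (70:30) evaluable children.

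**The case against.** The strongest reply is that {20b} names no test. The t-test and Mann-Whitney wording in {20a} sits under primary and secondary outcomes, and the form of a subgroup analysis is detail that a condensed article may leave to a fuller plan. This stands in part: testing within strata is an inference, and a plan not shown could contain an interaction model. It does not remove the mismatch, because the article states the hypothesis and fixes the tests, and the Abstract applies those tests to the data without qualification.

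It is also fair that the age hypothesis was stated in advance with a direction and a reason, that its cut-points are fixed, and that they are the randomisation strata. A reader might infer undisclosed searching through subgroups; the document does not support that. Pre-specification makes the age question more credible, but it does not supply a test of it.

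Two further readings go too far:

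- That the age question would be settled by chance, half the time wrongly. The 50% to 55% includes trials in which only the older group is significant, which would not support the hypothesis.
- That the trial would probably report a spurious subgroup. The 41% is below one half. It also assumes a test at 0.05 in every stratum, whereas {20a} gives 0.05 as the threshold for the primary outcome and none for subgroups. If several outcomes are analysed by subgroup the risk would be higher, but {20b} does not say so.

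Finally, the interaction test has low power and would rarely settle the question. That is true. The gain is an honest estimate with its uncertainty.

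**Conclusion.** The point holds in this form: the article states an effect-modification hypothesis, names only two-arm tests, lists age as one of eight subgroup factors without an interaction analysis, and sets no multiplicity control or exploratory label for those factors.

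If the named tests are applied within age groups, false support for the hypothesis arises in about 25% to 43% of trials in which both groups gain 0.5 points. This depends on the assumed age split and a common SD of 1.40. The 41% risk of at least one nominally significant stratum rests on about 17 strata, assumed stratum sizes, a 0.05 threshold and the primary outcome alone.

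The plan should be changed on this point, but it is no threat to the primary result.

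**What to change.** Add to {20b}:

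- One pre-specified treatment-by-age analysis: a linear model of post-procedural CFS with arm, age stratum (5–11, 12–17) and their interaction. Report the difference in effect between strata with a 95% CI, whichever test is used for the primary comparison. A separate model is needed because {20a} specifies a test and not a model to which a term could be added.
- A statement that power is low, about 25% to 29% for a 0.5-point difference, so that a non-significant interaction is not read as equal benefit.
- A statement that the other seven factors are exploratory, reported as interaction estimates with CIs and with no claims of significance within subgroups. There is added reason for this label: painkiller use and removal method are recorded after randomisation in an unblinded trial, and the fracture sites are picked from the trial's own data.

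The cost is one extra model, some wording and fewer subgroup claims. No change to sample size, data collection or procedures is needed.
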